**Methods:**

PerfectFit is a cluster randomized controlled trial, consisting of two arms. Based on cardiovascular risk profiling, done between 2012 and 2014, we included employees based on one or more risk factors and motivation to participate. One arm is the ‘limited’ health program (control) that consists of: (a) an HRA as a decision aid for lifestyle changes, including tailored and personalized advice, and pros and cons of the options, and (b) a newsletter every 3 months. The other arm is the ‘extensive’ program (intervention), which is additionally offered MI-sessions by trained occupational physicians, 4 face-to-face and 3 by telephone, and is offered more choices of health promotion activities in the HRA. During the follow-up period, participants choose the health promotion activities they personally prefer. After six and twelve months, outcomes will be assessed by online questionnaires. After twelve months the cardiovascular risk profiling will be repeated. The primary outcome is self-reported general health. Secondary outcomes are self-reported work ability, CVD-risk score, sickness absence, productivity loss at work, participation in health promotion activities, changes in lifestyle (smoking, alcohol consumption, physical activity, stress management) and body mass index. Furthermore, a process evaluation and an economic analysis will be performed.

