### Inclusion criteria for the study

Participants in this study were 40 years and older who presented with at least one CVD risk factor during the baseline cardio screening. The age group 40 years and older was chosen for two reasons. Firstly, cardiovascular risk scores such as the Framingham Risk Score [35] and the European SCORE function start at the age of 40. Secondly, cardio screening is mandatory for military personnel in this age group [36]. The screening was performed by the OPs of the participating health centres.

The cardio screening consisted of three components: (1) a short questionnaire with questions related to personal lifestyle and family history; (2) anthropometric measurements; and (3) blood measurements. In a face-to-face session, the OP provided “usual care”-advice according to the applicable Dutch guidelines [37].

The short questionnaire used in the cardio screening consisted of eight questions on health behavior such as smoking (yes, no); meeting the Dutch physical activity norm of exercising five times a week at moderate intensity for at least half an hour (yes, no); family and personal history of cardiovascular diseases (yes, no), such as suffering from atrial fibrillation (yes, no); a first degree family member with angina pectoris or a history of heart attack (yes, no); and ever being diagnosed with diabetes (yes, no) or hypertension (yes, no). Participants were also asked whether they were being treated with prescription drugs for hypertension or heart problems (yes, no).

For blood pressure, weight, height and serum measurements, the OPs or their assistants used the instruments that are available for their daily practice. These instruments could vary between OPs, but were the same throughout the study. Systolic and diastolic blood pressures (in mmHg) were measured twice in a seated position at rest, and average blood pressure values were used. Waist circumference was measured halfway between the lower rib and the iliac crest, as is advised by the Dutch obesity recommendations for general practitioners [38]. Serum was analysed for total cholesterol, HDL, LDL, triglycerides (mmol/l), and glucose (mmol/l). If the glucose level exceeded 11.1, then also HbA1c (%) was measured.

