These three components of the cardio screening provided entry points for the study, as it was used to identify employees at high risk for CVD. Inclusion criteria were met if a person had at least one of the following risk factors for CVD:Angina or myocardial infarction in first degree relatives;Physical inactivity, i.e. not meeting the guideline of physical activity at moderate intensity less than 30 min a day for 5 days per week or comparable effort;Smoking;Self-reported diabetes mellitus or random glucose ≥ 11.1 mmol/l;Obesity, defined as BMI ≥ 30 kg/m^2^ and / or waist circumference ≥ 102 cm for men or BMI ≥ 30 kg/m^2^ and/or ≥ 88 cm for women.Hypertension (diastolic value > 90 mm Hg or a systolic value > 140 mmHg) or the use of antihypertensive drugs;Dyslipidaemia (total cholesterol ≥ 5 mmol/l or LDL cholesterol ≥ 2.5 mmol/l or triglycerides: ≥ 1.7,mmol/l or HDL cholesterol: ≤ 1.0 mmol/l).

Employees who met the above mentioned inclusion criteria were excluded from participation if they had (1) manifest CVD (history of myocardial infarction, heart failure, or cerebrovascular accident); (2) a terminal illness; or (3) a history of psychosis. A flowchart of participants is shown in Fig. 1.

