### Study interventions

After the cardio screening at baseline, employees who were included in both the extensive and the limited study intervention groups, were invited by the OP to log on to the web-based HRA, by giving them a personal voucher-code.

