### Randomization, blinding, and allocation to interventions

Military bases, regional police forces, and hospital wards were randomly assigned as ‘clusters’ to one of the two intervention groups. A total of 18 clusters were randomized, which were equally divided in 9 clusters that were allocated to the limited intervention and 9 clusters that were allocated to the extensive intervention. In each of these clusters, one or more OPs were assigned to contribute to PerfectFit, based on shown interest. We chose for a cluster design to ensure that the OPs were only active within a single study arm. The organizational unit was the preferred cluster for two reasons. First, OPs from the same organizational unit were all trained to execute the intervention so that discussions among colleagues would not bias the results. Second, grouping participants from the same organizational unit into the same intervention group will prevent so-called “contamination effects” among participants, i.e., talking and sharing experiences about involvement in two different types of interventions, which might influence their behaviors [69, 70].

In the military force we constructed ten clusters consisting of military ground force army bases located in different regions in The Netherlands. Since the police force was facing a large reorganization with possible replacements of OPs from one organizational unit to another, only two clusters could be constructed, based on organizational units in different regions. Randomization in the academic hospital was performed at the ward level, creating a total of 6 clusters.

For all organizations, the OPs only perform work for the health center within that particular organizational unit. Clusters were ordered according to their sizes, i.e. the number of potential eligible participants. For each pair of clusters of similar size within one organization, one of the clusters was randomly allocated to the extensive intervention and the other to the limited intervention. Randomization took place after an OP from the unit had confirmed participation, and prior to the inclusion of individual participants. A researcher who was not otherwise involved in the trial used version 3.0.1 of The R Foundation for Statistical Computing for the randomization. Researchers, participating OPs, and participants were not blinded for the group allocation, since this was impossible given the nature of the intervention and the cluster design.

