## Results

### Baseline characteristics of participants

Figure 1 shows the CONSORT diagram [72] of the flow of clusters and participants through the first phases of the trial. In total, 9 clusters (*n* = 217), were assigned to the limited intervention (control), and 9 clusters (*n* = 274) to the extensive intervention (intervention). One cluster dropped out after randomization and before any cardio screenings were done, because the only OP within this cluster had other priorities in work. Three more OPs dropped out before any cardio screenings were done, two because of personal problems and one because she left her job. A total of 652 employees undertook the cardio screening. Based on these cardio screenings, 91.4 % (*n* = 598) were found to have risk factors for CVD, of whom 82.3 % were included (*n* = 493). Reasons for no inclusion were the presence of exclusion criteria or retirement or having to go abroad for work in the near future. For 16 participants the baseline questionnaire was missing, but we did receive blood- or anthropometric-measurements. The number of missings ranged from *n* = 1 (for the variable age) to *n* = 40 (for the variable level of education).

Baseline characteristics of participants in the three organizations are presented in Table 1. The military and police forces included a majority of males, whereas the hospital included mostly females. Among participants of the police force more than 76 % had a BMI higher than 25 kg/m2, and in the military force this percentage was 80.5 %. The percentage in the hospital of 46 % is lower and is similar to the average for the Dutch population.

Table 2 presents the baseline characteristics of the extensive intervention versus control study groups. The average age of the participants was 52, and 81.4 % were male. The randomization was successful in creating study groups with similar characteristics. Only for smoking a difference between the groups was found (*p* = 0.026). The CVD risk based on the Framingham score showed that more than 30 % of our study population is at intermediate or high risk, without differences in distribution between the two groups (*p* = 0.430).

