Our study design is unique for both its blended design of the intervention using a qualified decision aid and the follow-up at 6 and 12 months, which enables us to evaluate not just the initiation of health activities [9] but also the sustainability of lifestyle changes [81]. A second strength is the target population of employees in highly demanding jobs from three types of working organizations, whose workplace productivity and sickness absence might benefit from our intervention. Another strength is that the intervention is implemented within existing health centers and by their own OPs, improving external validity and making the results generalizable to larger companies. For the purpose of this study, a large investment was done for the OPs to master MI, which will remain beneficial to the organizations after completion of the study. Both the OPs from the extensive group and those from the limited group (after completion of the study), are educated to use the MI-technique, and skills they acquire and master during the time of the study and immediately afterwards can be internalized and incorporated in their everyday practice with all employees. From the perspective of the organization and society, these investments may pay off in the long run: an economic evaluation will be performed to analyze whether this truly is the case.

The study has three primary limitations. First, the effects on lifestyle changes may be affected by the healthy volunteer bias, since the study sample consists of employees of organizations who were actively recruited and who volunteered to participate [82]. Although we found differences in characteristics between organizations (Table 1), the potential bias will effect both the intervention and limited group alike, and will not have a large effect on our results (Table 2). Second, an attrition bias may occur at the follow-up measurements since those who achieve lifestyle changes might be more willing to do the final assessment than those who do not [83]. We will try to prevent this by sending personal invitations for final measurements by the OPs and having the OPs stimulate the participant to also fill out the questionnaire. A third issue is that blinding of the OPs, the participants and the investigators would have been preferred but could not be done in this real-life pragmatic trial.

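### Employees entered after unblinded cluster allocation, so the article's assurance that volunteer bias affects both arms equally is not secured by the design or supported by Table 2

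*Protocol article*

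**What the plan says.** On timing and masking, the protocol article (Randomization, blinding, and allocation to interventions) states: "Randomization took place after an OP from the unit had confirmed participation, and prior to the inclusion of individual participants". It adds: "Researchers, participating OPs, and participants were not blinded for the group allocation".

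On who handled entry, the section on inclusion criteria says "The screening was performed by the OPs of the participating health centres". The section on study interventions says that included employees "were invited by the OP to log on to the web-based HRA, by giving them a personal voucher-code".

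The entry conditions appear in three places:

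- Inclusion criteria for the study: employees with a risk factor "were excluded from participation if they had (1) manifest CVD", a terminal illness or a history of psychosis. Nothing else is listed.
- Abstract, Methods: "we included employees based on one or more risk factors and motivation to participate".
- Results, Baseline characteristics of participants: "Reasons for no inclusion were the presence of exclusion criteria or retirement or having to go abroad for work in the near future".

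On the consequence, the first limitation in the Discussion concerns healthy volunteer bias. It concludes that "the potential bias will effect both the intervention and limited group alike, and will not have a large effect on our results", with Table 2 as support. The Results section also says that randomization produced similar groups and that smoking alone differed.

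**The concern.** In a trial that randomizes individuals after consent, volunteer bias limits generalizability but leaves the comparison between arms intact, because everyone volunteers before the arm is known. Here the order is reversed. The arm was fixed at cluster level first, and employees then entered knowing, or able to know, what they were being offered. The offers differ: a web-based assessment with newsletters in one arm, and the same plus seven coaching sessions and more activity choices in the other. Willingness to join, and an OP's readiness to invite, could therefore depend on the arm.

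An intention-to-treat analysis of those included does not repair selection that occurs between allocation and inclusion. If selection differed by arm, the general-health contrast would mix the program effect with differences in who entered. A reader who accepts the Discussion sentence would set this aside without examining it.

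**Working it through.** **1. Non-inclusion after a positive screen** (Results, Baseline characteristics of participants)

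- Inputs: 652 screened, 598 with a risk factor, 493 included.
- Stated inclusion 82.3%; recomputed 493/598 = 82.4%, which agrees apart from rounding.
- Not included: 598 − 493 = 105, and 105/598 = 17.6%.
- The same section gives 217 + 274 = 491 by arm, while Table 2 heads its columns 218 + 275 = 493. With 491, non-inclusion is 107/598 = 17.9%.

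**2. What the pooled figure can show**

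The text does not split the 105 by arm. As an assumption, take splits (limited/extensive) from 20/85 to 85/20, with 218 and 275 included:

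- 20/85: 20/238 = 8.4% against 85/360 = 23.6%.
- 85/20: 85/303 = 28.1% against 20/295 = 6.8%.

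The pooled 17.6% is compatible with equal or very unequal non-inclusion, in either direction.

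**3. Entry conditions side by side**

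| Condition | Inclusion criteria section | Abstract | Results |
|---|---|---|---|
| Manifest CVD, terminal illness, psychosis | yes | no | yes (as exclusion criteria) |
| Retirement | no | no | yes |
| Work abroad soon | no | no | yes |
| Motivation to participate | no | yes | no |

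**4. Table 2 as support for equal selection**

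Recomputed with Pearson chi-square without continuity correction, and a two-sample t-test for age:

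| Characteristic | Limited | Extensive | Printed p | Recomputed p |
|---|---|---|---|---|
| Age, mean | 52.1 | 50.7 | <0.006 | 0.007 (t = 2.72) |
| Organization: military | 27.6% | 40.1% | 0.007 | 0.007 (χ² = 9.80, 2 df) |
| Male | 77.0% | 84.6% | 0.036 | 0.036 (χ² = 4.41, 1 df) |
| High education | 21.2% | 33.7% | 0.011 | 0.011 (χ² = 8.96, 2 df) |
| Smoking | 11.1% | 18.6% | 0.026 | 0.025 (χ² = 5.05, 1 df) |

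The organization and education tests cover all three categories. The age gap fits rounding of the means and SDs. Five characteristics differ at p < 0.05, not smoking alone. These tests ignore clustering, so they describe imbalance and do not prove differential entry. Table 2 also covers only those included, so even perfect balance there could not establish equal selection on motivation.

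**5. Possible size, on assumed inputs only**

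Suppose inclusion were 77% in one arm and 87% in the other, and the extra employees let in differed by 5 to 10 points on the 0–100 general-health scale. They would make up 0.10/0.87 = 11.5% of the fuller arm and shift its mean by 0.115 × 5 = 0.57 to 0.115 × 10 = 1.15 points. Reading the planned 10% difference as 10% of 71 = 7.1 points, that is 8% to 16% of it. Neither input comes from the article, so this shows scale and is not an estimate.

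**The case against.** Retirement and a posting abroad look administrative. Both arms need questionnaires at 6 and 12 months and a repeat cardiovascular screening at 12 months, and several outcomes concern work. Such employees are hard to follow in either arm. Motivation may mean little more than voluntary consent. The Discussion sentence concerns healthy volunteer bias only, and lack of blinding is listed separately as a limitation. General health is measured at baseline, and the primary model is a repeated-measures mixed model adjusted for confounders, which may absorb part of any entry difference. Figure 1, not available here, may already give non-inclusion by arm. That OPs decided on inclusion is an inference from their screening and inviting.

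Most of this stands, and it limits the point. A reader might infer from 217 against 274 included, or 60 against 110 in the military, that the filters worked unequally and kept out people who could not attend coaching. The documents do not support that. Such a filter would shrink the extensive arm, yet the military has more inclusions there. The counts also reflect screening uptake, the lost military cluster and the withdrawal of OPs before screening began. The Table 2 differences may partly share one source: Table 1 shows military participants to be younger, almost all male and more often highly educated than police participants, and the extensive arm has more of them.

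None of this supplies grounds for saying that volunteer bias acts equally on both arms. Adjustment for measured covariates does not cover motivation that varies with the offer.

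**Conclusion.** The point holds as a limit on what the article may claim. Entry followed unblinded allocation, 105 of 598 at-risk employees (17.6%) were not included, some reasons lie outside the listed criteria, and motivation could depend on the arm offered. The statement that volunteer bias is equal across arms and has no large effect is therefore unsupported by the design, and the table cited for it shows five differences.

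It does not follow that entry did differ by arm. Neither the existence, the direction nor the size of a bias can be established from the article. How many of the 105 were left out for retirement or work abroad is not stated in the text.

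**What to change.** 1. Replace the Discussion sentence with a statement that inclusion followed unblinded cluster allocation, so that volunteer and other selection may differ by arm. Align the claim that only smoking differed with Table 2.
2. Reconcile the three accounts of entry: state whether retirement, work abroad and motivation were entry conditions in addition to the listed criteria, and whether they were applied in the same way in both arms.
3. Report the non-included employees by arm and reason, if Figure 1 does not already do so.
4. Add a sensitivity analysis of the primary model with inverse-probability-of-inclusion weights, estimated by arm among the 598 at-risk screened employees from the cardio-screening values (such as blood pressure, BMI, waist, lipids and smoking). Where data on non-included employees may not be used, give bounds from the counts by arm. State that neither approach removes selection on unmeasured motivation.

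The cost is some rewording, at most one table and one extra analysis, with no new data collection. The weighted interval will probably be somewhat wider, and the claim of comparability becomes weaker.

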## Discussion

The PerfectFit study aims to establish whether adding MI to a web-based HRA is a key-factor for improving effectiveness in changing unhealthy lifestyles and reducing risk factors for chronic diseases. MI is known to improve BMI, total blood cholesterol, systolic blood pressure, and blood alcohol concentration [73]. By adding MI, this superiority RCT combines the advantages of an online personalized and tailored approach with the advantages of a face-to-face approach, thus aiming to improve participation and sustained effectiveness of workplace health promotion programs [74].

Web-based healthcare (eHealth) is receiving growing attention since it can tailor interventions to target population characteristics (e.g., specific risk factors), thereby facilitating wider access and encouraging self-care, and possibly reducing health-care costs and improving efficacy [75]. However, a proven feature of eHealth is that its effect decreases after the intervention has been completed [15]. Our blended approach of adding MI to a web-based HRA is promising in several ways. First, we expect an increase of lifestyle changes, since previous research showed dose–response relationships between exposure to an intervention (number and duration of exposures) and behavior change outcomes [73, 76]. Second, it may lead to a higher sustainability of these lifestyle changes, since there is evidence that providing face-to-face counselling with a higher number of overall contacts was associated with greater short and long-term effectiveness [76]. MI has a large potential to fill the gap between the intention to change and the actual behavior change, commonly referred to as the intention-behavior gap [77]. This potential was previously demonstrated for lifestyle changes such as physical activity and a healthy diet [78–80]. MI is a unique tool for evoking and strengthening intrinsic motivation for a more sustainable change in lifestyle [13–19].

Our study design is unique for both its blended design of the intervention using a qualified decision aid and the follow-up at 6 and 12 months, which enables us to evaluate not just the initiation of health activities [9] but also the sustainability of lifestyle changes [81]. A second strength is the target population of employees in highly demanding jobs from three types of working organizations, whose workplace productivity and sickness absence might benefit from our intervention. Another strength is that the intervention is implemented within existing health centers and by their own OPs, improving external validity and making the results generalizable to larger companies. For the purpose of this study, a large investment was done for the OPs to master MI, which will remain beneficial to the organizations after completion of the study. Both the OPs from the extensive group and those from the limited group (after completion of the study), are educated to use the MI-technique, and skills they acquire and master during the time of the study and immediately afterwards can be internalized and incorporated in their everyday practice with all employees. From the perspective of the organization and society, these investments may pay off in the long run: an economic evaluation will be performed to analyze whether this truly is the case.

The study has three primary limitations. First, the effects on lifestyle changes may be affected by the healthy volunteer bias, since the study sample consists of employees of organizations who were actively recruited and who volunteered to participate [82]. Although we found differences in characteristics between organizations (Table 1), the potential bias will effect both the intervention and limited group alike, and will not have a large effect on our results (Table 2). Second, an attrition bias may occur at the follow-up measurements since those who achieve lifestyle changes might be more willing to do the final assessment than those who do not [83]. We will try to prevent this by sending personal invitations for final measurements by the OPs and having the OPs stimulate the participant to also fill out the questionnaire. A third issue is that blinding of the OPs, the participants and the investigators would have been preferred but could not be done in this real-life pragmatic trial.

The equal distribution of health factors of our participants between both the intervention and control groups, suggests that we will be able to evaluate the intervention-effects with minimal adjustments. Although there is no statistical difference in BMI between the groups, the percentages of participants that are overweight (BMI > 25 kg/m2) exceeds 70 % in both groups, which is high compared to 47 % within the general population [84]. This is in line with previous research reporting increasingly high percentages of overweight and obesity in the military force [85] and in police officers [86]. However, we are cautiously interpreting overweight in population groups that are doing physically demanding work, since it is well known that muscular type of body composition might lead to higher BMI [87]. Therefore, in our study we also rely on the waist circumference, in order to have an accurate estimation of obesity.

Dyslipidemia, another risk-factor for CVD, exceeds 90 % within both study groups, which could be caused by our strict cut-off value for LDL-cholesterol (>2.5 mmol/l). Nevertheless, since we found that a majority of our participants has more than 1 inclusion criteria and that over 30 % has intermediate or high Framingham risk scores, we can assume that changes in health behaviors can tackle these health and occupational hazards. Actual lifestyle changes will be measured and will also be related to the intention to change at baseline, which will give us a more accurate picture of the participants’ intention-behavior gap.

To keep the workforce vital and productive, there is a growing need for effective and affordable health promotion strategies which can also be easily implemented. A key component of this study is MI, which has several elements that promise to be beneficial for both participants and healthcare providers. MI is a well-described and practical approach that respects individual choices and leads to an increased responsibility for their own health [24, 40]. By adding counselling sessions using MI in the intervention group, participants will be involved in a shared decision making-process related to their lifestyles. We hypothesize that, once participants discover their inner strengths and motivations, their health-behavior gains will be more sustainable and will be maintained over time [15]. Upcoming papers will assess to what extent this hypothesis can be confirmed and whether this blended care approach is an essential strategy for future health promotion programs.

